
### Participant timeline

Information on enrolment, intervention, and assessment in the trial can be found in Table 2.

**Table 2 Tab2:** Enrolment, interventions, and assessments of the MCCP

	Study period				
	Enrolment	Allocation	Pre-treatment	Post-treatment	Follow-up
	− *T*_1_	*T*_0_	*T*_1_	*T*_2_	*T*_3_
Eligibility screening	X				
Informed consent	X				
Randomization		X			
Allocation		X			
Socio-demographics		X			
Job-related characteristics		X			
**Interventions**					
Treatment			X	X	
Waiting list			X	X	
**Assessments**					
Burnout			X	X	X
Depression symptoms			X	X	X
Anxiety symptoms			X	X	X
Post-traumatic symptoms			X	X	X
Insomnia			X	X	X
Perception of stress			X	X	X
Mindfulness skills			X	X	X
Self-criticism and self-reassurance			X	X	X

Primary and secondary outcomes will be measured at baseline (T1), at the end of the intervention (T2), and 1 month after the end of intervention (T3). Adverse events and untoward effects will be assessed during each treatment. Table 1 contains a summary of all the measures in the trial.

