### Outcomes

As the proposed intervention aims to mitigate the prolonged strain on hospital staff by working with the most severe or critical COVID-19 patients, burnout—a specific indicator of chronic work-related dysfunctional response—was selected as the main outcome of interest. In particular, any change in the sub-subscale of emotional exhaustion (EX) between pre-treatment and 1-month post-treatment was chosen as the primary outcome of burnout [37]. Emotional exhaustion is a psychological construct that explores the perception of physical and emotional fatigue. It is characterized specifically by a lack of energy required to handle daily life and the prevalence of feelings of apathy and emotional detachment at work. It is the central dimension in burnout [38] and correlates strongly with job performance, absenteeism, higher psychopathological risk, and poor organizational effectiveness [39]. Numerous studies have found EX in HCWs to be associated with acute depressive symptoms, anxiety disorders, sleep problems, and poor quality relationships with patients [1, 33–35].

The secondary outcomes of the intervention will be to observe any change between pre-treatment and post-treatment and between pre-treatment and 1-month post-treatment, in:Professional efficacy (MBI-GS) [37]Cynicism (MBI-GS) [37]Depressive symptoms (PHQ-9) [40]Anxiety symptoms (GAD-7) [41]Post-traumatic symptoms (IES-R) [42]Insomnia (ISI) [43]Perception of stress (PSS) [44]Mindfulness skills (FFMQ) [45]Evaluation of self-criticism and self-reassurance (FSCRS) [46]

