### Assignment of interventions: allocation

Participants will be randomly allocated to the intervention or the WL control group with an allocation ratio of 1:1. Participants allocated to the experimental group will receive the intervention immediately after randomization, and those assigned to the control group will be offered the same intervention 6 months after. The experimental intervention will take place over 6-weeks. The pre-test, post-test, and 1-month follow-up will be carried out at the same time for both study groups.

The trial statistician will prepare the sequence of treatments randomly permuted into blocks of 2. The randomization schedule will be generated with Stata software (version 17.0; Stata Corp, Corp, College Station, TX, USA) using the ‘ralloc’ command for random allocation of treatments balanced in blocks. The Emotional Exhaustion sub-scale (EX) score of the MBI-GS assessed at the screening phase will be used to perform a stratified randomization based on the median value (EX ≥ median vs. EX< median). Two lists of randomizations will be generated according to the levels of the stratification variable. The trial statistician will communicate by email the randomization results to the responsible for trial, who will notify to the participants by email if they belong to the intervention or the WL control group.

The trial will begin in September 2022. Enrolment will end as soon as the expected number is reached (36 for the intervention group and 36 for the control group). Before the intervention, participants randomly assigned to the intervention group will be divided into three subgroups consisting of 12 individuals. Each subgroup will follow the mindfulness courses (led by the same instructor) for 6 weeks. The courses will be delivered every Monday for subgroup 1, Tuesday for subgroup 2, and Wednesday for subgroup 3. Nurses will attend the intervention during working hours as part of the continuing professional education (CPE) courses provided by the Verona Hospital Trust Administration.

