### Assignment of interventions: blinding

Participants will be screened by an independent psychologist after completing the MBI-GS. The randomization will be independently conducted by the trial statistician. The assessments pre-treatment, post-treatment, and at 1-month post-treatment will be completed online. The participants and the treatment psychologist will not be blind.

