### Statistical methods

Statistical analysis will be based on an intention-to-treat (ITT) basis, comparing outcomes from all nurses allocated to the two trial arms. Findings will be reported according to the CONSORT guidelines for parallel-group randomized trials [47].

Personal socio-demographic information and job-related characteristics will be summarized descriptively according to the treatment arms. Categorical data will be presented as frequencies and percentages. Means, standard deviations, medians, interquartile ranges, and minima and maxima will be presented for continuous data. To verify the success of randomization, the baseline characteristics of the two treatment groups will be compared: continuous variables will be compared with a *t*-test (for normally distributed variables) or the Mann-Whitney *U* test (for non-normally distributed variables). Categorical variables will be evaluated with the chi-square or 2-tailed Fisher exact test. Change scores will be calculated. Data will be presented as percentages for categorical data and means and standard deviations for continuous data; 95% CIs will be used to indicate uncertainty around the estimates.

Follow-up data will be analysed using mixed models to establish the correlation between repeated measurements and examine main effects and their interaction, adjusting for the baseline score. The presence of multi-collinearity, interaction, and higher power terms will be assessed to check final model validity. Statistical significance will be defined at two-sided *p* < .05. All analyses will be carried out using Stata 17.0 for Windows.

The effects of baseline covariates expected to have an important influence on the primary outcome will be controlled for by comparing covariate-adjusted analyses with unadjusted analyses. Certain covariates that will be considered at baseline will refer to demographic variables (e.g. gender, age, and education level), the organizational context, and participation in non-mindfulness support courses.

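### Table 2 schedules the outcome baseline (T1) after allocation, and nothing ensures that unblinded nurses complete it before they are told their arm

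*Protocol article*

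**What the plan says.** - **Order of events.** Participant timeline, Table 2, runs from enrolment (−T1) to allocation (T0, with rows for "Randomization" and allocation), then pre-treatment (T1), post-treatment (T2) and follow-up (T3). Burnout and all other outcome scales have their first mark at T1.
- **T1 is the baseline.** The text under the table opens "Primary and secondary outcomes will be measured at baseline (T1), at the end of the intervention (T2" and adds a third measurement one month later (T3).
- **Primary outcome.** In Outcomes, the change in EX "between pre-treatment and 1-month post-treatment was chosen as the primary outcome of burnout". Table 3 in the Appendix ends the change at post-treatment instead. Both versions start at pre-treatment, so the difference does not affect this point.
- **Model.** Statistical methods plans mixed models to "examine main effects and their interaction, adjusting for the baseline score".
- **Disclosure and blinding.** The statistician sends the randomisation result to the person responsible for the trial, "who will notify to the participants by email if they belong to the intervention or the WL control group". The blinding section adds: "The participants and the treatment psychologist will not be blind". The allocation section has the pre-test done at the same time in both study groups.
- **An EX score from before randomisation exists.** It is taken at screening, sets eligibility (2.20 or more) and defines the randomisation stratum (above or below the median). It is not named as the baseline for the change or for adjustment.

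**The concern.** EX is self-reported. The respondents are nurses selected for exhaustion, and in the scheduled order they may already know whether they start the course now or are offered it 6 months later. Disappointment on the waiting list or relief in the intervention arm could move T1 EX apart between the arms before any treatment is given. Randomisation protects only what is measured before allocation can influence it. Subtracting or adjusting for a score that allocation has already moved carries that movement into the treatment effect.

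Two further consequences follow from the same order. Nurses who skip T1 because they know their arm would be missing in a way related to allocation. And the baseline tests planned to verify the success of randomisation, if applied to T1 scores, could not tell chance imbalance from a reaction to allocation.

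**Working it through.** **1. The plan's own figure.** Inputs from Sample size: difference −1.21, SD 1.8, 36 per arm, two-sided 0.05, equal-variance t-test. SE = 1.8 × √(2/36) = 0.424. Noncentrality = 1.21/0.424 = 2.85 on 70 df. Power = 80.3%, which reproduces the stated 80%.

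**2. Bias from a shifted T1.** Let s be the amount by which knowing the arm raises mean T1 EX on the waiting list relative to the intervention arm. Suppose the reaction has gone by T3.
- Change score: expected estimate = −1.21 + s, so the bias is s.
- Adjusted for T1: expected estimate = −1.21 + b·s, where b is the T3-on-T1 slope. With equal SDs, b equals the correlation ρ.

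**3. Precision.** The documents give neither ρ nor s; both are assumed. Read 1.8 as the SD of EX at each visit and take ρ = 0.5.
- Change-score SD = 1.8 × √(2 × (1 − 0.5)) = 1.8.
- Adjusted residual SD = 1.8 × √(1 − 0.25) = 1.559; SE = 1.559 × √(2/36) = 0.367 on 69 df.

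**4. Results for diluting shifts** (power against the two-sided 0.05 test)

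| Assumed s | Adjusted estimate | Adjusted power | Change-score estimate | Change-score power |
|---|---|---|---|---|
| 0 | −1.21 | 90% | −1.21 | 80% |
| 0.1 | −1.16 | 88% | −1.11 | 73% |
| 0.3 | −1.06 | 81% | −0.91 | 56% |
| 0.5 | −0.96 | 73% | −0.71 | 38% |

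**5. Dependence on ρ.** At s = 0.3, ρ from 0.3 to 0.7 gives an adjusted bias of 0.09 to 0.21.

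**6. Other direction and the null.** If s has the opposite sign, the same amounts are added to the effect: at 0.3, the adjusted estimate would be −1.36. With no true effect, a shift of 0.3 in either direction raises the rejection rate from 5% to about 7% (adjusted) or 11% (change score).

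**7. Carry-over.** If a fraction k of the reaction persists to T3, the adjusted estimate departs from −1.21 by s × (ρ − k). This is smaller than in the table for small k, and it changes sign once k exceeds ρ.

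**8. With a baseline taken before allocation,** s is zero by design, whatever the nurses' later reaction. The stated inputs, 36 per arm and 80.3% power, stay as they are.

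**The case against.** The strongest reply is that the decisive step is inferred. No sentence says that T1 is answered after the allocation email. The allocation section gives the notification no timing relative to the T1 questionnaire, and Data collection and management says only that nurses above the screening cut-off enter the study and complete the assessments online. This stands: Table 2 supports T1 being after randomisation but does not settle that it is after notification. It does not remove the point, because the table fixes an order that permits the problem and no other text prevents it.

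The size is also open to challenge. No shift has a source in the documents, and burnout is described there as a chronic response, which an email may hardly move. In the adjusted analysis, power at a shift of 0.3 is still about 81%, in line with the planned 80%. The change-score losses are larger, but the planned inferential model adjusts for baseline, and change scores are only said to be calculated. All of this stands.

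Three stronger readings are tempting, and the documents do not support them:
- **That nurses without a T1 score drop out of the analysis and intention-to-treat fails.** Statistical methods provides for multiple imputation, without limiting it to follow-up scores. What remains is that non-completion prompted by knowing the arm strains the missing-at-random assumption.
- **That the screening EX score is used only for stratification.** It also sets eligibility.
- **That the screening score is ready to serve as the baseline for everyone.** The password that links questionnaires is first created at the baseline evaluation, and the survey is called anonymous, so linkage to T2 and T3 is not assured. The MBI-GS is the only outcome scale named at screening.

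**Conclusion.** The point holds as a design risk that the plan leaves open. By Table 2, the score that starts the primary change and serves for baseline adjustment comes after allocation in an open waiting-list trial, and the protocol has no safeguard that it precedes disclosure of the arm. If allocation shifts T1 and the reaction has faded by T3, the bias is the full shift in a change score and about the T1–T3 slope times the shift in the adjusted model.

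How large this would be, and in which direction, cannot be known from the documents. The fall in adjusted power from about 90% to 88%, 81% and 73% rests on assumed diluting shifts of 0.1, 0.3 and 0.5, an assumed correlation of 0.5 and no carry-over. A reader might infer that the trial is certain to be biased, or biased towards no effect; neither follows. The case for acting is that the risk can be removed at almost no cost before enrolment.

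**What to change.** **Preferred.** Have nurses complete the full T1 battery after consent and screening and before randomisation. At the least, release the allocation email only once T1 has been submitted. State the order in the text and redraw Table 2 to match. If T1 is already meant to be completed first, correcting the table and adding one sentence is enough.

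**Cost.** An online battery of about 30 minutes moves earlier; sample size and stated power are unchanged. If T1 precedes randomisation, nurses who do not complete it are not randomised, which is a small loss at recruitment.

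**Fallback, for the primary outcome only.** Use the screening EX score as the baseline for the change and as the covariate, provided the linking password is created at screening so that the score can be matched to T2 and T3. Selection at 2.20 or more brings regression to the mean into a change from screening, but equally in both arms, so the comparison between arms is not biased by it. The secondary outcomes outside the MBI-GS would still have no value from before randomisation, which is why moving T1 is the better choice.

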## Methods

### Trial design

A randomized controlled trial (RCT) parallel group waiting list design will be used to assess the efficacy of a mindful and compassion programme for nurses (superiority trial) (Table 3 in Appendix). Participants will be randomly assigned to one of two groups: the experimental group will receive the Mindful Compassion Care Program (MCCP) [32, 35], and the control group will be allocated to a waiting list (WL) with an allocation ratio of 1:1. The effectiveness of the experimental intervention will be assessed by comparing the changes in the level of burnout at the end of the treatment and after 1-month later (this follow-up interval has been set due to organizational and time constraints). Other psychological dimensions will also be investigated (i.e. anxiety and depressive symptoms, posttraumatic symptoms, insomnia, perception of stress, mindfulness skills and evaluation of self-criticism and self-reassurance).

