If participants of either group report any adverse events during the trial, this will be registered in the electronic database system. Serious adverse events will be reported to the ethics committee. If participants require additional mental health support, they will be referred to the regular services, but it is also possible for participants to consult with an appointed psychologist if they so request or if the trainer so advises.

Each session will focus on topics that will be explored through specific exercises, presented by a licensed psychologists with demonstrated experience in the application of mindfulness-based protocols and who meets the criteria of the internationally agreed good practice guidelines of the UK network for mindfulness-based teachers.

If a given participant at the end of the trial continues to display high or higher levels of distress, they will be referred to the Psychiatric Consultation Service at the UOC of Psychosomatics, Verona Hospital Trust. This service has provided an individual help pathway for HCWs with psychological distress since the beginning of the pandemic. The WL is the control group planned for this study. It will remain in place for the entire period of the intervention. Details on the rationale of the study are shown in the flowchart (Fig. 1).

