### Sample size

Sample size calculation was performed a priori according to the primary outcome on an intention-to-treat basis. A total of 72 nurses (36 nurses per treatment condition) achieves 80% power to reject the null hypothesis of equal means when the population mean difference is − 1.21 with a standard deviation for both groups of 1.8 and a significance level of 0.05 using a two-sided two-sample equal-variance *t*-test (PASS 2021). Both the expected mean change and the standard deviation were found by exploring data (which are available from the authors) regarding the distress of nurses working in COVID-19 wards [1, 4].

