### Oversight and monitoring

As has been noted, participants who experience (serious) adverse events and harm resulting from the intervention or those allocated in the waiting list who experience a worsening of their mental health status will be referred to the Psychiatric Consultation Service at the Psychosomatics Unit and the project management group; they, however, will be excluded from the study. The ethics committees will be also informed.

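### Adverse-event ascertainment is described differently in three places and, on the natural reading, differs by arm, so any between-arm account of harms would be open to ascertainment bias

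*Protocol article*

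**What the plan says.** Three sections of the protocol article deal with how adverse events come to notice.

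- **Participant timeline, text after Table 2:** "Adverse events and untoward effects will be assessed during each treatment". This is the only sentence that describes active assessment. Table 2 has no adverse-event row at any time point.
- **Interventions:** "If participants of either group report any adverse events during the trial, this will be registered in the electronic database system". This rule is set off by a report, is worded alike for both arms and covers the whole trial.
- **Oversight and monitoring:** the section names (serious) adverse events and harm resulting from the intervention on one side. On the other, "those allocated in the waiting list who experience a worsening of their mental health status will be referred to the Psychiatric Consultation Service". Both kinds of participant are also to be excluded from the study.

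On contacts, Trial design says that "the control group will be allocated to a waiting list (WL) with an allocation ratio of 1:1". Interventions gives the MCCP arm six regular sessions and one all-day class. No study session is described for the waiting list during that period. The online assessments are common to both arms: "The pre-test, post-test, and 1-month follow-up will be carried out at the same time for both study groups".

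**The concern.** If events are asked about at sessions, and one arm has no sessions, the two arms have different chances of having the same event recorded. A difference in counts could then reflect detection rather than harm. More contacts usually find more events, so the programme would probably look worse than it is.

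This matters here because the Discussion describes the sample as being at raised risk of psychiatric comorbidity and the literature on harm from mindfulness programmes as sparse. Comparable harms data from the two arms would be useful, and the control arm is where worsening without treatment would be seen.

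There is a second consequence. Oversight and monitoring links a recorded event or worsening to exclusion from the study. If detection differs by arm, exclusions may differ too, and they would be related to mental state. Each excluded nurse is 1/36 = 2.8% of an arm.

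**Working it through.** **The plan's own figure.** The only design calculation is the sample size: "A total of 72 nurses (36 nurses per treatment condition) achieves 80% power to reject the null hypothesis of equal means". With a difference of 1.21, SD 1.8 and 36 per arm, the noncentrality is 1.21 / (1.8 × √(2/36)) = 1.21 / 0.4243 = 2.85. The exact two-sided t-test at 0.05 then has power 80.3% (79.2% at 35 per arm), so the figure reproduces. It concerns emotional exhaustion, and the present point does not depend on it.

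**What each treatment means.** Two readings are possible.

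1. *Each treatment session.* The sentence stands under Table 2, whose Interventions block has one row called Treatment and another called Waiting list. In that section the word treatment does not include the waiting list. On this reading active assessment occurs at up to seven MCCP contacts and at none in the control arm.
2. *Each arm.* Elsewhere the article uses treatment for both arms, as in Statistical methods: "the baseline characteristics of the two treatment groups will be compared". On this reading controls are included, but the sentence gives no contact or time point at which they are asked.

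On either reading, assessment during treatment does not clearly extend to the month between T2 and T3.

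**Coverage on the first reading.**

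| Period | MCCP | Waiting list |
|---|---|---|
| T1 to T2 | Active assessment at sessions, plus reports | Reports |
| T2 to T3 | Reports | Reports |
| Trigger in Oversight and monitoring | Adverse events and harm from the intervention | Worsening mental health |

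**Size, under assumptions only.** The document gives no event rate and no detection rate. Assume the same true risk p in both arms, full capture in MCCP, and waiting-list capture equal to a fraction s of that.

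- Expected recorded events: 36p in MCCP and 36ps in the waiting list.
- Apparent risk ratio: p/(ps) = 1/s. Apparent risk difference: p(1 − s).

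| p | s | MCCP events | Waiting-list events | Risk difference | Risk ratio |
|---|---|---|---|---|---|
| 10% | 30% | 3.6 | 1.1 | 0.07 | 3.33 |
| 10% | 50% | 3.6 | 1.8 | 0.05 | 2.00 |
| 10% | 80% | 3.6 | 2.9 | 0.02 | 1.25 |
| 20% | 30% | 7.2 | 2.2 | 0.14 | 3.33 |
| 20% | 50% | 7.2 | 3.6 | 0.10 | 2.00 |
| 20% | 80% | 7.2 | 5.8 | 0.04 | 1.25 |

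The ratio depends on s alone and only returns the assumption. The table shows what unequal capture could do; it does not estimate what will happen.

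**The case against.** The case on the other side is substantial, and much of it stands.

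- *A reader might infer that events are assessed only in the MCCP arm and that waiting-list nurses must volunteer them unprompted.* Neither is written. The article does not say only, the phrase about each treatment can cover both arms, and the rule under Interventions is the same for both groups without saying whether reports are prompted. This stands. The point rests on the more natural reading, not on an explicit statement.
- *A reader might infer that the trial's harms comparison is biased.* Adverse events are not among the listed outcomes, and Statistical methods describes no between-arm test or estimate for them. This stands. The risk is conditional on someone comparing the arms.
- *Worsening is already measured.* Depression, anxiety, post-traumatic symptoms, insomnia and stress are scored at T1, T2 and T3 at the same times in both arms. For average symptom change this stands. It does not settle event recording, because nothing links a change in score to an event record or to the worsening named under Oversight and monitoring. Data collection and management also calls the survey anonymous, linked by a password that the participant creates.
- *Exclusion after an event conflicts with intention to treat however events are detected.* This stands. It is a neighbouring inconsistency, and unequal detection would only make it differ by arm.
- *How events are elicited is detail that an article leaves to the full protocol.* This stands for a missing table row on its own. It does not remove the difference between three statements that the article does make.

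**Conclusion.** The point holds as an inconsistency that creates an avoidable risk. The three sections do not describe one method of ascertainment. On the natural reading, active assessment happens at contacts that exist only in the MCCP arm. The control arm, and both arms after T2, rest on reports.

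Any between-arm description of harms would then be open to ascertainment bias. The direction is probably against MCCP, but this is not certain: the waiting-list trigger of worsening needs no link to a cause, whereas the other trigger refers to harm from the intervention, so counts based on those triggers could lean the other way.

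The size cannot be computed from the document. The range of 3.33 to 1.25 for the apparent risk ratio rests wholly on assumed waiting-list capture of 30% to 80% of MCCP capture, with equal true risk. A claim of, say, a three-fold spurious excess would only restate assumed detection rates (90% against 30% gives 3) and should not be quoted as a finding.

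The primary comparison of emotional exhaustion is not touched by ascertainment itself. It could be affected only through the exclusion rule, which has to be reconciled in any case.

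**What to change.** 1. Add the same brief adverse-event and worsening item to the T2 and T3 online questionnaires in both arms, with the same recall period, and add that row to Table 2.
2. Base any between-arm summary of harms on those common time points. Report events noted in sessions separately, for the MCCP arm, as descriptive information.
3. Reword the sentences under Interventions, after Table 2 and under Oversight and monitoring so that they describe one method, the same in both arms and running through T3.
4. Reconcile the exclusion under Oversight and monitoring with the intention-to-treat statement under Statistical methods, which covers all nurses allocated. The text should say what exclusion means for the data of those nurses. Which referral or withdrawal rule is appropriate is a clinical matter outside this point.

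The questionnaires already exist and are completed by both arms at these times, so no extra staff or visit is needed. The cost is a slightly longer survey. One limit remains: common items at T2 and T3 make the arms comparable but do not detect events in the control arm as they occur between those points.
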